**ABSTRACT**

**Rationale**: While varenicline on its own is the most effective medication for smoking cessation, long-term abstinence is still relatively poor. The addition of tDCS as an adjunct to pharmacotherapy is a novel approach but one that is grounded in a growing evidence-base.

**Research Question/Objective**: The primary objective of this research is to provide preliminary evidence of the effectiveness of tDCS as an adjunct treatment to pharmacotherapy for smoking cessation. Does the addition of active tDCS to the left DLPFC improve the effectiveness of varenicline in the treatment of tobacco dependence? Does it make individuals more resistant to relapse in the long-term?

**Study Design**: Double-blind, sham-controlled, randomized clinical trial

**Setting**: A free Nicotine Dependence Clinic in downtown Toronto, Canada

**Participants**: Fifty daily dependent adult smokers seeking treatment to quit smoking

**Intervention and Procedures**: Twelve weeks of varenicline treatment plus tDCS (active: 20 minutes at 2 mA OR sham: 30 seconds at 2 mA, 19.5 minutes at 0 mA), daily (M-F) for the first 2 weeks and then every 2 weeks for the next 10 weeks. 2 FMRI scans at baseline and 1 scan at end-of-treatment. Eye-tracking viewing tests will be conducted at baseline, week 4, week 8,end-of-treatment and at 6 months follow up. Follow-ups at 6-months. A monetary delayed discounting task will be performed at baseline, end of treatment and at 6 months follow up.

**Measurements**: Expired CO, self-reported smoking, and subjective craving and withdrawal at each study visit, weekly self-reported smoking status (7day PPA) from end of treatment to 6 months. For fMRI: BOLD activation, perfusion, structural T1 mapping, DTI and functional connectivity. For Eye-tracking: attentional bias to substance-related cues, attentional bias to negative emotional cues and attentional bias to high-arousal/high-risk cues.

**Potential Impact**: For every two smokers who quit, one life is saved from a tobacco-related mortality. Therefore, even a small improvement in smoking cessation treatment effectiveness and long-term abstinence would decrease the prevalence of tobacco-related death and disease and save the health care system billions of dollars.

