**METHODS**

**Design**

This will be a double-blind sham-controlled two-arm randomized clinical trial. Fifty participants will be randomized (1:1) to each arm. Arm 1 will be active tDCS plus varenicline (n=25) and Arm 2 will be sham tDCS plus varenicline (n=25). Treatment duration will be 12 weeks. Subjects will be required to attend an in person assessment visit. They will then be randomized to a condition. Neuroimaging scans (fMRI) and eye-tracking tests will be conducted in all participants at baseline. Participants will undergo two scans at baseline on different days within the same week: one in a satiated state and one in a non-satiated state. The same tasks will be performed at each scan. s. Following the baseline fMRI scans and eye-tracking tests, subjects will start taking the varenicline simultaneous with starting the tDCS regimen whereby they will come to the clinic every day (Monday to Friday) for the first 2 weeks to undergo the stimulation (active: 20 minutes at 2mA, sham: 30 seconds at 2mA and then nothing). Their target quit date will be at the end of this 2 week period. They will return to the clinic every two weeks for the next 10 weeks for a booster tDCS session and to complete questionnaires. Eye tracking tests will be conducted at the end of the fourth and eighth weeks. At the end of the 12-week treatment period they will undergo a third fMRI scan and eye-tracking tests. For the next 14 weeks they will be contacted weekly by e-mail or text message to report on their smoking status as measured by the 7 day point prevalence abstinence question. “Have you had a cigarette, even a puff, in the last 7 days?” At the 6-month time point subjects will be asked to return to the clinic for a brief visit to confirm smoking abstinence using expired CO and urinary cotinine and to complete questionnaires.

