**Procedures**

Following the initial assessment appointment to obtain consent and confirm eligibility, the first tDCS treatment session will be booked. A breathalyser will screen for alcohol and expired CO at each tDCS session. The tDCS stimulation will take place in a quiet room, free of distractions. Stimulation will continue uninterrupted for 20 minutes with the experimenter in the room. While being stimulated, subjects will be required to read self-help materials related to smoking cessation, relapse prevention, and mood management. The readings for each day of stimulation will be standardized for all subjects.

To increase the opportunity to detect an acute beneficial effect of tDCS, participants will be asked to refrain from smoking for 2 hours prior to the start of each treatment session. Relative CO readings from the first day (ad lib smoking) compared to subsequent days will provide a coarse means of verifying compliance with the 2-hour pre-session smoke-free requirement.

Participants will be randomly assigned (1:1) to one of 2 treatment arms (double-blind). Participants will be matched as closely as possible on age, gender and cigarettes per day.

There will be 10 consecutive daily sessions of tDCS with the anode over the left DLPFC and cathode over the right DLPFC (active or sham) (Monday-Friday for 2 weeks; 2 mA x 20 min). Participants assigned to sham will have electrodes placed identically to active but receive only 30 seconds active stimulation. Participants will also be videotaped during each tDCS session to ensure consistency of tDCS application between research personnel and for documenting participant reactions during the session. This will also be used to document any side effects/complications participants may experience during the session. Each video tape session, as well as all data collected in the trial, will be stored on a secure server and will be retained for 10 years after the participant completes the study, as suggested by CAMH’s policy on Storage of Records. After each tDCS session, the video footage will be transferred from the camera to the secure server.

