**Outcome Measures**

The primary outcome measure will be continuous abstinence from smoking during weeks 9 – 12 as reported at clinic visits during those 4 weeks and confirmed using expired CO. Subjects will be classified as treatment responders if they respond “no” to the question: Have you smoked any cigarettes (even a puff) in the last seven days?

The key secondary outcome measures are:

1. Self-reported 7 day point prevalence abstinence throughout weeks 2 to 12 confirmed by expired CO at each clinic visit. To calculate survival curves we will also collect self-reported continuous abstinence weeks 9 through 26. For weeks 13 to 25, this will be collected via email or text message. For week 26, subjects will attend a brief clinic visit so abstinence can be confirmed with expired CO and urinary cotinine using a semi-quantitative dipstick. We hypothesize that the active tDCS group will have higher rates of abstinence (less relapse) than the sham tDCS group.

2. fMRI: change in Blood Oxygen Level Dependent (BOLD) activation in brain regions known to be associated with drug craving and emotion processing/regulation. MRS: GSH levels measured in a single voxel placed over prefrontal cortex. Fractional anisotropy (FA) values will be extracted from DTI analysis from regions of interest (ROIs) or to form probabilistic tractography for the whole brain. Network maps will be extracted and analyzed from the resting state functional connectivity measure.

3. Eye Tracking tests: changes in attentional bias to smoking-related cues and negative emotional cues. Attentional bias to high-arousal/high-risk cues.

*Self-Report Measures*

Participants will complete the 10-item Questionnaire of Smoking Urges-Brief (QSU-10; Tiffany and Drobes, 1991) and the Minnesota Nicotine Withdrawal Scale (MNSW; Toll et al, 2007) at each treatment session upon arrival and immediately after tDCS. They will complete a Side Effects Checklist ([name] et al., 1995) at the end of each treatment session.

Trait scales to be completed at baseline will include the FTND (Heatherton et al 1991) and Alcohol Use Disorders Identification Test (Saunders et al., 1993), 90-day Alcohol Timeline Followback (TLFB; Sobell and Sobell, 1992); 30-day Tobacco Timeline Followback (adapted from alcohol TLFB); Sensation Seeking Scale (Zuckerman et al., 1978).

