**Data Analysis**

Continuous data (cravings, mood, cigarettes smoked/day, CO) will be assessed with 2 Gender x 2 (Laterality) x 10 (session) Analyses of Variance (ANOVA). Parallel ANOVAs will assess self-report measures during post-treatment follow-up. Categorical data (e.g., # abstinent participants/session) will be assessed with chi-square, and Kaplan-Meyer survival analysis for repeated measures. Planned comparisons will be performed for the critical experimental conditions (active tDCS) vs. sham.

The critical metric will be Effect Size (partial η2 generated by SPSS), rather than p level. This will reveal the degree of efficacy for the primary outcome variable, Consecutive Days Abstinent (small = .01, medium = .06, large = .14), and allow us to estimate N required to achieve statistical significance for this effect (80% power, α = .05, two-tailed). Pearson correlations will explore the possible relationship between effects of tDCS (session 10 scores, controlling for session 1) and trait factors (e.g., FTND, age, gender, depression).Analysis of MRI data

For the neuroimaging data, brain imaging measures will be compared between groups and across time points, using analysis of variance. MRI measures will also be related to subjective responses (i.e., baseline scores and changes in craving, mood, and withdrawal) using linear regression.

fMRI data will be analyzed by fitting a general linear model (GLM) to the data time-series at every voxel across the brain (and/or within ROIs) and assessing effects using F/t-tests and % signal change calculations. Quantitative T1 maps and DTI analysis will be analyzed at the whole brain level and using ROIs.

After back-sorting by treatment outcome (achieved/maintained abstinence), we expect baseline measures to predict relapse, and active tDCS treatment to result in more efficient functional activation, . than sham tDCS at the second MRI scan.

Analysis of Eye-Tracking Data

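### The session ANOVA counts pre-treatment session-1 readings as an outcome level and does not adjust active versus sham for them, which can cost power and lower partial eta-squared on the supportive continuous measures

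*Protocol*

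**What the plan says.** - **Timing.** Protocol, Design: "subjects will start taking the varenicline simultaneous with starting the tDCS regimen whereby they will come to the clinic every day". Procedures: "There will be 10 consecutive daily sessions of tDCS". Whatever is read on arrival at session 1 therefore precedes both tDCS and varenicline.
- **What is collected.** Outcome Measures has craving and withdrawal scored "at each treatment session upon arrival and immediately after tDCS". Procedures: "A breathalyser will screen for alcohol and expired CO at each tDCS session". The Abstract lists "Expired CO, self-reported smoking, and subjective craving and withdrawal at each study visit".
- **First-day CO.** Procedures already uses it as a reference: "Relative CO readings from the first day (ad lib smoking) compared to subsequent days" serve as a coarse check on the two-hour smoke-free rule.
- **Analysis.** Data Analysis assigns cravings, mood, cigarettes per day and CO to "2 Gender x 2 (Laterality) x 10 (session) Analyses of Variance". The ten levels match the ten daily sessions, so session 1 is an outcome level. Active versus sham appears in a separate sentence as a planned comparison, and no covariate is named.
- **Baseline control elsewhere.** The same section relates tDCS effects to trait factors using "session 10 scores, controlling for session 1".

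**The concern.** The protocol treats session 1 as a baseline in the exploratory correlations but as an outcome in the analysis of the randomised groups. If the arms are compared on the average of all ten sessions, two things follow. One tenth of an average of on-arrival readings cannot carry a treatment effect. And the most useful predictor of a person's later craving, CO and smoking goes unused, so stable differences between people remain in the error term.

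At stake are power and effect size for the continuous measures. Partial eta-squared, the protocol's chosen metric, depends on the error term, so reporting an effect size instead of a p-value does not avoid the problem.

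**Working it through.** **The protocol's own power figure.** Sample Size and Power Calculation gives 40% versus 80% abstinence, 25 per arm, alpha 0.05 and 80% power. A two-sided normal approximation needs 23 per arm without continuity correction and 28 with it. At 25 per arm, power is 84.5% by that approximation and 78.8% by Fisher's exact test. The figure reproduces. No power is stated for the session ANOVA.

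**Inputs.** From the protocol: 25 per arm, alpha 0.05 two-tailed, 10 sessions. Assumed, because the protocol gives neither: between-session correlation r, and a standardised arm effect d = 0.5 that is zero on arrival at session 1 and constant from session 2. Outcome SD is 1, correlation is equal between sessions unless stated, and the Gender factor is ignored.

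**Formulas.** Power is from the noncentral t distribution with noncentrality (effect/SD) × √(25/2).
- Ten-session mean, unadjusted: effect 0.9d, variance r + (1 − r)/10, 48 df.
- Sessions 2–10, unadjusted: effect d, variance v9 = r + (1 − r)/9, 48 df.
- Sessions 2–10 minus session 1: effect d, variance v9 + 1 − 2r, 48 df.
- Sessions 2–10 with session 1 as covariate: effect d, variance v9 − r², 47 df.
- Arm-by-session term: noncentral F with 9 and 432 df, noncentrality (25/2) × Σ(m − m̄)²/(1 − r), where m is the arm effect at each session.

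**Worked case, r = 0.5.**
- As written: 0.45/√0.55 = 0.607.
- Adjusted: v9 = 0.5 + 0.5/9 = 0.5556; 0.5556 − 0.25 = 0.3056; 0.5/√0.3056 = 0.905.
- Ratio of sample sizes for equal power: (0.905/0.607)² = 2.2.
- Partial eta-squared, as D²/(D² + 4) with D the standardised difference: 0.084 as written, 0.170 adjusted.

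**Power, constant effect of 0.5 SD from session 2**

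| r | Ten-session mean | Sessions 2–10, unadjusted | Change from session 1 | Sessions 2–10, adjusted | Arm-by-session |
|---|---|---|---|---|---|
| 0.3 | 72.7% | 80.5% | 50.2% | 89.7% | 22.2% |
| 0.5 | 55.7% | 64.2% | 64.2% | 87.9% | 31.1% |
| 0.7 | 44.6% | 52.5% | 85.1% | 93.9% | 52.1% |

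The ten-session mean needs 1.6, 2.2 and 3.7 times the participants of the adjusted analysis. At r = 0.7, partial eta-squared is 0.065 against 0.204. Dilution is the smaller part: moving from the second column to the third gains about 8 points, and adjustment supplies the rest. At r = 0 only dilution is left (sample-size ratio 1.11).

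**Other assumptions.**
- AR(1) correlation, ten-session mean against adjusted: 68% against 80% at 0.7, and 45% against 81% at 0.9.
- Linear build-up to 0.5 SD at session 10, equal correlation. Ten-session mean, adjusted mean and arm-by-session term: 21.5%, 41.3% and 35.3% at r = 0.5; 17.4%, 49.6% and 58.5% at r = 0.7.

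**The case against.** - **No decisive term is named.** Data Analysis does not say that active versus sham is a main effect over ten sessions. A reader might take the ten-session-mean column as the power of the plan. The document does not support that. The arm-by-session term uses session 1 as a within-person reference and, under a gradual build-up, can match or beat the adjusted mean. A gradual build-up is credible, since the target quit date falls at the end of the daily sessions. A planned change-from-session-1 contrast would also narrow the gap at r of 0.5 or more; at r = 0.3 it is weaker than the ten-session mean. This objection stands and makes the loss conditional.
- **The printed model has no arm factor.** It has Laterality, although Procedures and tDCS describe one electrode placement for both arms. This stands, and the fix has to deal with it.
- **The outcomes are supportive.** A reader might infer that the flaw spoils the planning of the next trial. It does not: Data Analysis ties the required N to Consecutive Days Abstinent, and the measures here are neither the primary nor listed key secondary outcomes.
- **Not all session-1 data are pre-treatment.** Craving and withdrawal are also scored after stimulation, and Procedures looks for an acute benefit. Session 1 is a legitimate outcome for those scores. The point covers on-arrival readings only.
- **Covariates usually belong in the SAP.** That would answer a missing detail. Here the protocol itself fixes the factors and the ten levels, and so places session 1 among the outcomes.
- **Correlation and effect are assumed.** True. The direction holds for the main effect across the range tried; the size does not carry over.

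**Conclusion.** The point holds in a limited form. On-arrival session-1 values precede treatment, yet they enter the session ANOVA as an outcome level and are not used to adjust active versus sham, while the same section adjusts for session 1 elsewhere.

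If the arms are compared by a main effect over all ten sessions, the assumed 0.5 SD effect loses about 17 points of power at r = 0.3, 32 at r = 0.5 and 49 at r = 0.7 under equal correlation, and about 12 under AR(1) at 0.7. Partial eta-squared falls with it. Most of the loss comes from not adjusting, not from the 10% dilution. If a different term decides the comparison, the loss can be smaller or absent. The primary abstinence analysis is untouched. The change is still worth making, because the value is already collected and the adjustment costs almost nothing.

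**What to change.** In Data Analysis, replace the description of the session ANOVA along these lines:

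- For each continuous measure read on arrival, the session-1 on-arrival value is a covariate, sessions 2 to 10 are the outcome, and treatment arm (active versus sham) is the between-subject factor in place of Laterality.
- For craving and withdrawal scored after stimulation, session 1 stays in the outcome and the session-1 on-arrival score is the covariate.

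This brings the randomised comparison into line with the session-1 control already applied in the trait correlations. It costs one sentence and one degree of freedom, needs no new data and does not alter trial conduct.

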**Participants**

Study participants will be 50 treatment seeking daily dependent smokers willing to make a quit attempt in the next 30 days. They will be recruited from our Nicotine Dependence Clinic and from the Greater Toronto Area through paid advertising in local newspapers and through the CAMH Registry and the CAMH website. Participants will have no concurrent Axis I psychiatric disorder (or history of substance use disorder), based on SCID, and be free of psychoactive drugs and medications, based on self-report and urinalysis. To ensure against subtle neurological deficits associated with sub-clinical alcohol misuse, men will be required to drink no more than 12 standard drinks per week and women will be required to drink no more than 9 drinks per week. These values conform to safe drinking limits for non-problem drinking (Sobell and Sobell, 1992). According to standard protocols for tDCS clinical trials, participants will also be excluded if they: a) have had recent clinically significant head trauma; b) have a history of seizures and/or epilepsy; c) are pregnant or planning to become pregnant; d) have pacemakers or implanted electrical devices such as cochlear implants; e) have metal embedded in the skull; or f) have skin lesions, open wounds, bruising, or similar injuries at either of the stimulation sites.

*Eligibility Criteria*

- Male or female
- Ages 19-65
- Daily smoker > 8 CPD
- Seeking treatment to quit smoking
- No current/recent DSM-IV Axis I diagnosis (apart from nicotine dependence)
- No current use of psychoactive drugs or medications
- No current use of Nicotine Replacement Therapy, e-cigarettes, or other medications for smoking cessation
- No history of seizures/epilepsy
- No metal embedded in the skull and/or implanted electrical devices
- No head injury (no concussion – diagnosed by a physician; OR no blow to the head with loss of consciousness for more than 1 hour)
- No known contraindications to fMRI
- No known contraindications to Varenicline
- Able to attend daily appointments for tDCS for the first 2 weeks and then once every 2 weeks for the next 10 weeks.
- Willing to undergo three fMRI scans – two at baseline and another at the end of treatment.

**Procedures**

Following the initial assessment appointment to obtain consent and confirm eligibility, the first tDCS treatment session will be booked. A breathalyser will screen for alcohol and expired CO at each tDCS session. The tDCS stimulation will take place in a quiet room, free of distractions. Stimulation will continue uninterrupted for 20 minutes with the experimenter in the room. While being stimulated, subjects will be required to read self-help materials related to smoking cessation, relapse prevention, and mood management. The readings for each day of stimulation will be standardized for all subjects.

To increase the opportunity to detect an acute beneficial effect of tDCS, participants will be asked to refrain from smoking for 2 hours prior to the start of each treatment session. Relative CO readings from the first day (ad lib smoking) compared to subsequent days will provide a coarse means of verifying compliance with the 2-hour pre-session smoke-free requirement.

Participants will be randomly assigned (1:1) to one of 2 treatment arms (double-blind). Participants will be matched as closely as possible on age, gender and cigarettes per day.

There will be 10 consecutive daily sessions of tDCS with the anode over the left DLPFC and cathode over the right DLPFC (active or sham) (Monday-Friday for 2 weeks; 2 mA x 20 min). Participants assigned to sham will have electrodes placed identically to active but receive only 30 seconds active stimulation. Participants will also be videotaped during each tDCS session to ensure consistency of tDCS application between research personnel and for documenting participant reactions during the session. This will also be used to document any side effects/complications participants may experience during the session. Each video tape session, as well as all data collected in the trial, will be stored on a secure server and will be retained for 10 years after the participant completes the study, as suggested by CAMH’s policy on Storage of Records. After each tDCS session, the video footage will be transferred from the camera to the secure server.

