DTI is a widely used MRI technique for measuring water diffusion within specific areas of the brain by quantifying the intensity of each image element, which in turn, reflects the rate of water diffusion. DTI is a useful measure for identifying white matter microstructures and has been shown to significantly alter brain tractography in adult smokers in areas such as the corpus callosum (Paul et al., 2008, Hudkins et al., 2012, Lin et al., 2012). DTI will be used to test for significantly tractography and/or white matter differences that may exist between active tDCS vs sham.

Resting state functional connectivity (rsFC)

rsFC is a task-independent measure of brain activity that is based on correlations between low frequency fluctuations of BOLD signal between brain regions in the absence of an explicit task (Biswal et al., 1995). Smoking has been shown to affect rsFC in the ventral and dorsal striatum, the insula and limbic systems (Ding et al., 2013, Janes et al., 2012, Sweitzer et al., 2016). rsFC data will be used to evaluate if there are differences in rsFC between active tDCS and sham and also if these rsFC networks are correlated with quit at end of treatment.

*Brain structure:* Structural MRI studies have identified cortical thickness, white matter, and volumetric abnormalities in smokers in cerebellum, striatum, cingulate cortex, prefrontal cortex, and insula using voxel-based morphometry (VBM) (see (Azizian et al, 2009) for review), and these, in turn, relate to cigarette exposure and craving (Morales et al, 2014). Quantitative T1-weighted MRI measures (qMRI) can shed additional light on the tissue microstructure underlying these findings, and allows for quantification (rather than only visualization) of results. These measures will be used to assess and detect subtle brain tissue alterations in both grey and white matter before and after tDCs treatment and/or smoking cessation. These neuroimaging parameters have never been assessed for changes resulting from abstinence from smoking nor have they been assessed in the context of tDCS treatment.

Each MRI scan will be preceded by an assessment of withdrawal, mood, and craving (Questionnaire of Smoking Urges (QSU; Tiffany & Drobes, 1991); POMS (Profile of Mood States)). Breathalyzer tests and urine samples will be collected at all scans to confirm abstinence from alcohol and other drugs of abuse prior to scans

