**Participant compensation**

Participants will be compensated as follow: $20 for baseline assessment (1), $20 per tDCS visit (15 total sessions), $95 per fMRI scans (3 sessions total) and $50 for 6 month follow up visit (1).

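### The 2-hour smoke-free instruction before every tDCS session also covers the week 10 and 12 visits, where expired CO is the only biochemical confirmation of the primary outcome

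*Protocol*

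**What the plan says.** Three parts of the Protocol meet here.

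- **Procedures.** Before each session, "participants will be asked to refrain from smoking for 2 hours prior to the start of each treatment session". The stated reason is to improve the chance of seeing an acute tDCS effect. On measurement, "A breathalyser will screen for alcohol and expired CO at each tDCS session". The same section adds: "Relative CO readings from the first day (ad lib smoking) compared to subsequent days will provide a coarse means of verifying compliance".
- **Design and Participant compensation.** After the two weeks of daily sessions, "They will return to the clinic every two weeks for the next 10 weeks for a booster tDCS session and to complete questionnaires". Compensation is set for 15 tDCS sessions.
- **Outcome Measures.** The primary outcome is "continuous abstinence from smoking during weeks 9 – 12 as reported at clinic visits during those 4 weeks and confirmed using expired CO". Urinary cotinine, by semi-quantitative dipstick, is planned only for week 26.

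Urine is also taken at the end-of-treatment scan, but for another purpose (Neuroimaging): "Breathalyzer tests and urine samples will be collected at all scans to confirm abstinence from alcohol and other drugs of abuse". No section gives a CO cut-off.

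**The concern.** One CO reading is asked to do two jobs. In Procedures, a reading below that of the ad lib first day is evidence that the participant obeyed the 2-hour rule. In Outcome Measures, CO at weeks 10 and 12 is what should expose someone who claims abstinence but still smokes. For such a person, obeying the rule lowers the value meant to detect the smoking. The Protocol's own use of CO as a compliance check concedes the direction of the effect.

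False passes would occur in both arms. They raise both abstinence rates and pull them together, which matters in a pilot meant to inform a larger trial. Their frequency could not be recovered afterwards, because no other marker of smoking is planned at the end of treatment.

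**Working it through.** **1. Which visits the rule covers.** Ten daily sessions (Monday to Friday for 2 weeks), then boosters every 2 weeks for 10 weeks: weeks 4, 6, 8, 10 and 12. The total is 10 + 5 = 15, which reproduces the count in Participant compensation. The treatment visits inside weeks 9–12 are therefore weeks 10 and 12. These weeks are inferred from the schedule; the Protocol does not name them.

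**2. Loss of CO in 2 hours.** Assume exponential decline with half-life *h*, so the fraction remaining is r = 2^(−2/h). The half-life and the 10 ppm cut-off are assumptions, since the documents give neither.

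| h (hours) | r | CO lost | Level that falls to 10 ppm (10/r) |
|---|---|---|---|
| 3 | 0.630 | 37% | 15.9 ppm |
| 4 | 0.707 | 29% | 14.1 ppm |
| 5 | 0.758 | 24% | 13.2 ppm |
| 6 | 0.794 | 21% | 12.6 ppm |

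**3. Whose result changes.** The rule matters only for someone who still smokes, answers that they have not, follows the instruction, would not have gone 2 hours without smoking anyway, and lies between 10 ppm and the last column. Below that band the person passes with or without the rule; above it the person still fails. The documents size none of these groups.

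**4. Effect on the difference.** Sample Size and Power Calculation takes 40% against 80% with 25 per arm and 80% power. That figure reproduces: the pooled two-sided formula needs 23 per arm, and at 25 per arm power is 84.5% (chi-square) or 78.8% (Fisher).

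If a share *f* of non-abstainers passes in both arms, a true rate p is observed as p + f(1 − p), and the difference becomes (p₂ − p₁)(1 − f). Each percentage point that the rule adds to *f* therefore takes 0.4 points off a 40-point difference. As an illustration only, suppose the rule adds 1 to 3 points, starting from f = 0:

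- f = 0.01: 40.6% vs 80.2%, difference 39.6 points
- f = 0.03: 41.8% vs 80.6%, difference 38.8 points

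For scale, the 95% margin on that difference is 1.96 × √(0.4×0.6/25 + 0.8×0.2/25) = 1.96 × 0.1265 = about ±25 points.

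**The case against.** **Self-report comes first.** CO only catches false claims of abstinence, so it is not the sole check on the outcome. That stands; it is the only biochemical one.

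**The rule has a purpose at boosters.** It is there to help detect an acute tDCS effect, and craving and withdrawal scores are taken before and after tDCS at every treatment session. For people still smoking, the rule standardises time since the last cigarette. This stands as a cost of lifting it. However, the analyses in Data Analysis use 10 sessions, and the correlations use session 10 controlling for session 1. These match the daily sessions and would be untouched.

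**The text may have been written with the daily sessions in mind.** Calling the first day ad lib sits awkwardly with a rule for each session. Nothing exempts the boosters, though, and if that was the intention one clause settles it.

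**Another reading may exist.** The Abstract lists expired CO at each study visit. If the end-of-treatment scan falls on a separate day, a CO value outside the rule may be available. The Protocol neither says so nor ties the primary outcome to it.

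**A stronger reading is tempting and should be resisted.** A reader might infer that the rule greatly enlarges the next trial. Taking 40% vs 60% and false-pass rates of 10% or 20%, observed rates become 46% vs 64% or 52% vs 68%, and N per arm rises from 97 to 119 or 146. The documents do not support charging that to this rule, for three reasons:

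- Those rates are total false passes. Comparing them with zero supposes that without the rule no continuing smoker would ever pass. On the same formula, a rule that adds 1 to 3 points to zero gives 99 to 103.
- The 60% is not the Protocol's figure.
- Data Analysis bases the future N on partial η² for Consecutive Days Abstinent, for which no CO confirmation is stated.

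**Conclusion.** The point holds as an overlap between Procedures and Outcome Measures that weakens the only biochemical confirmation of the primary outcome. The direction follows from the Protocol's own use of CO. The size is unknown and probably modest: under an assumed 3 to 6 hour half-life and 10 ppm cut-off, it is confined to false reporters between 10 and about 12.6 to 15.9 ppm. The instruction is the same in both arms, so the expected result is slight inflation of both abstinence rates and slight dilution of the difference, with no reason to expect one arm to be favoured. No figure for a larger future N should be attached to it. It is worth correcting because the correction is cheap and the information cannot be obtained later.

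**What to change.** 1. Reconcile Procedures with Outcome Measures. Either limit the 2-hour instruction to the ten daily sessions up to the quit date or, if it is kept at boosters, record time since last cigarette at weeks 10 and 12 beside the CO value.
2. Run the dipstick already planned for week 26 on the urine collected at the end-of-treatment scan, and record any other nicotine use that day. Entry excludes current nicotine replacement and e-cigarettes, but later use would otherwise be scored as smoking. This step assumes that a 2-hour gap does not move cotinine as it moves CO; the documents do not address that.
3. Report the primary outcome with and without cotinine confirmation. Anyone without a scan sample keeps the CO-confirmed status, so that responder status does not depend on attending the scan.

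**Cost.** One sentence in Procedures, one nicotine-use question and up to 50 dipsticks. Lifting the rule makes booster craving scores less standardised in people still smoking. The scan urine does not cover week 10, and its timing relative to the week 12 session is not stated. Observed abstinence rates may be slightly lower.
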